### Study setting

The study will be carried out in the Nanoro health district, a rural area located in the center of Burkina Faso, at 85Km from Ouagadougou, the capital city. The health district of Nanoro covers an area of 150,000 inhabitants and comprises 18 dispensaries, all with maternity, general clinic, and immunization programs (EPI) [30]. The main local language is Mooré, though French is the official language and almost 80% of adults have a cell phone [31]. The Clinical Research Unit of Nanoro (CRUN) has set up the Nanoro Health and Demographic Surveillance System (HDSS) in this geographical area since February 2009. The HDSS currently covers 24 villages in Nanoro district, including over 60,000 inhabitants. Through the HDDS, every household as well as every inhabitant in the district has a unique identification number with GPS coordinates. The surveillance activities consist in visiting every household 3 times a year to collect data on vital events such as births and deaths, as well as migration, pregnancies, pregnancy outcomes, household assets, and access and use of key disease control interventions. HDSS provides also the core research framework for cohort studies and intervention trials [31]. Nanoro belongs to the Sudan-Sahel zone, with an estimated 58,868 recorded malaria cases in 2015 [30]. Oral quinine is used for the treatment of uncomplicated malaria in pregnancy in the first trimester while artemether-lumefantrine (AL) or DHA-PQ are recommended in the second and third trimesters of pregnancy [32].

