### Intervention description

In this study, 2 packages will be used as comparators: the standard of care package versus the new intervention package.

The current standard of care strategy for pregnant women attending ANC during the second and third trimester of pregnancy is based on three components (standard RDTs, AL, and scheduled visits without reminder).

The new intervention package will include three components (US-RDTs, DHA-PQ, and phone call reminders). Each of these three components has been shown to individually improve pregnancy outcomes. We hypothesize that a synergistic action of the three components will result in a higher impact on the outcomes of interest (placental malaria infection, low birth weight, and peripheral malaria infection at delivery) as compared to the current standard of care.

Comparisons will not be done between the individual components of each intervention package, but rather their combined effects between study groups: the intervention group (ultrasensitive malaria RDTs, DHA-PQ, and phone reminder) and the control group (the standard of care described above which includes standard RDT, AL, and scheduled visit without reminder).

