#### Intervention group

Prior to each IPTp-SP dose administration, a blood sample will be collected for malaria infection screening using US-RDT and microscopy, Hb measurement, and filter paper confection for parasite genotyping. The date of the next IPTp-SP administration will be planned accordingly and the sequences repeated until delivery. Pregnant women with a positive US-RDT will be treated with a full course of DHA-PQ over 3 days. The first dose will be administered under direct observation during ANC and the subsequent doses of the intervention on days 2 and 3 will be taken unsupervised at home. The treatment observance will be assessed by the field worker at the end of the treatment. In addition, a questionnaire on health and socio-demographic characteristics will be administered as well as a physical examination. A phone call as a reminder will be made 1 week prior to the scheduled date for the second dose of IPTp-SP. If the participant is not reachable, the field worker will visit the household in order to remind the visit date. The objective is to increase the number of IPTp-SP doses per woman.

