The secondary clinical outcomes are pilot endpoints to include incidence rates (mean hemoglobin and birth weight), molecular and parasitological endpoints, safety, determinants of poor coverage of IPTP-SP, vector control effectiveness, and adverse events. Adverse events and serious adverse events will be monitored, managed, and recorded during the study. All study participants who receive at least one dose of the study drug will be included in the safety analysis. They will be recorded and tabulated for each treatment group. All parasitological data will be included in the parasitological analyses. For the evaluation of placental malaria and low birth weight in newborns, logistic regression will be performed while for the evaluation of the occurrence of malaria cases in pregnant women during the follow-up, Poisson regression will be implemented. The stratification or adjustment factors will be among others: the number of doses of IPTg-SP, the season of malaria transmission, and the gravidity. A statistical model will be used for the phone reminder by adjusting the number of calls (0, 1, 2) that the woman in the intervention group received before coming to this ANC. In this model, the number of calls for women in the control group will be 0. For the qualitative study, the acceptability will be assessed through focus group discussion and in-depth interviews. Topics covered by the in-depth interviews will comprise many components such as experience and opinions of the trial intervention groups, perceptions of the acceptability of the trial intervention, and implications for implementation. The interview guide will be used to collect data from pregnant women, health care workers, community health care workers, and traditional healers. The theoretical framework of acceptability developed by Mandeep Sekhon, Martin Cartwright, and Jill J. Francis will be used to assess acceptability. In this study, we will analyze the acceptability through the dimension of the burden, ethical consequences, experience, opportunity cost, intention, and affective attitude. The analysis will focus on the barriers and factors limiting adherence to IPTp-SP uptake.

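### The planned call-count model cannot estimate a reminder effect: number of calls is not randomised, is non-zero in one arm only, and overlooks home-visit reminders

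*Protocol article*

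**What the plan says.** All references are to the protocol article.

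- **Exposure (Statistical methods).** "A statistical model will be used for the phone reminder by adjusting the number of calls (0, 1, 2"), counting the calls "that the woman in the intervention group received before coming to this ANC". For controls: "In this model, the number of calls for women in the control group will be 0". The outcome of this model is not named.
- **Reminder procedure (Participant timeline, Intervention group).** "A phone call as a reminder will be made 1 week prior to the scheduled date for the second dose of IPTp-SP". The fallback is in person: "If the participant is not reachable, the field worker will visit the household in order to remind the visit date". The stated aim is more IPTp-SP doses per woman.
- **Phone access (Study setting).** In the study area "almost 80% of adults have a cell phone".
- **Rule on components (Intervention description).** "Comparisons will not be done between the individual components of each intervention package, but rather their combined effects between study groups". The intervention package joins the reminder with ultrasensitive RDTs and DHA-PQ, and none of the three is given to controls.
- **Related data (Primary feasibility outcomes).** The number of IPTp-SP doses is already monitored in both groups.

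**The concern.** Randomisation protects the comparison of group with group. It does not protect a comparison of women who received two calls with women who received one or none, because that number is settled after randomisation. It depends on whether the phone is answered, and possibly on how the woman attends.

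Three difficulties follow. The call count is confounded within the intervention group. It is tied to group, and so to the other two components. And the in-person reminder, which replaces the call, does not appear in it.

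At stake is what the pilot reports about the reminder. The Discussion section says that the pilot will inform the main trial, and a coefficient per call looks like a dose-response result. Readers may take it as evidence for or against the reminder when the design cannot supply that evidence.

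**Working it through.** The protocol gives no figure for this model, so there is none to reproduce. One figure is borrowed for the illustration, 152 women per group, and it does reproduce (two-sided 5%, 80% power, 40% against 25%, pooled variance under the null):

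n = [1.960·√(2·0.325·0.675) + 0.842·√(0.40·0.60 + 0.25·0.75)]² / 0.15² = (1.298 + 0.550)² / 0.0225 ≈ 152.

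**Step 1. What the coefficient measures.** Let g be group (1 = intervention) and c the number of calls. There are two ways to fit the model:

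- A: logit P(Y) = α + γc
- B: logit P(Y) = α + βg + γc

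In A, c > 0 occurs only when g = 1, so γ takes up whatever differs between the groups, including screening and DHA-PQ. In B, controls have g = 0 and c = 0 and inform only α. All information on γ then comes from intervention women who received different numbers of calls, which is a non-randomised contrast. Neither γ is the effect of the reminder.

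**Step 2. The zero code.** Controls are 0 by rule. A woman who could not be phoned and was visited at home has received no call, so on the natural reading she is also 0. If a fraction f of the intervention group is reminded only by visit, the reminded share of all zeros, with equal groups, is f/(1 + f). The protocol does not give f. Phone ownership of almost 80% among adults suggests values around 0.2 as an assumption:

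- f = 0: none
- f = 0.2: 0.2/1.2 = 17%
- f = 0.3: 0.3/1.3 = 23%

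**Step 3. Illustration under stated assumptions.** There were 152 women per group and 300 simulated trials per setting. The outcome was binary uptake with logit −0.8, that is 31%, near the 31.5% with at least three doses in the Introduction. A latent reluctance score (standard normal) lowers the logit of uptake by a slope of 0, 1 or 1.5. The logit of a second call is −0.8 plus a slope of 0, 1 or 1.5 times the score. The fraction not phoned was 0, 20% or 30%, independent of reluctance. The true group effect was a log odds ratio of 0 or 0.8 and belongs to the group. The number of calls itself has no effect in any setting.

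Ranges run over the three fractions not phoned. The slopes in the first column are for uptake / second call.

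| Slopes | True group log OR | OR per call, A | OR per call within intervention group (B) | OR by group |
|---|---|---|---|---|
| 0 / 0 | 0 | 0.99–1.00 | 0.97–1.02 | 0.99–1.00 |
| 1 / 0 | 0 | 1.00–1.01 | 0.99–1.01 | 1.01–1.02 |
| 1 / 1 | 0 | 0.88 | 0.48–0.81 | 0.98–1.02 |
| 1.5 / 1.5 | 0 | 0.79–0.82 | 0.28–0.71 | 0.99 |
| 0 / 0 | 0.8 | 1.46–1.64 | 0.99–1.01 | 2.21–2.29 |
| 1 / 0 | 0.8 | 1.39–1.50 | 0.99–1.01 | 1.95–1.98 |
| 1 / 1 | 0.8 | 1.23–1.28 | 0.48–0.82 | 1.95–1.96 |
| 1.5 / 1.5 | 0.8 | 1.08–1.10 | 0.29–0.70 | 1.77–1.78 |

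Three things can be read off.

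- **Package carried by calls.** In the fifth row calls do nothing, yet A gives 1.46 to 1.64, because calls stand in for group. B gives about 1.0 on data generated the same way. The answer depends on whether a group term is included, which the protocol does not say.
- **Home visits coded 0.** In the same row, A falls from 1.64 with nobody visited to 1.53 at 20% and 1.46 at 30%.
- **Confounding.** If reluctance both lowers uptake and brings more calls, A falls below 1 when there is no effect, and B falls further. The comparison by group stays near 1. Its decline from about 2.2 to 1.8 when there is a benefit is the usual shrinkage of a marginal odds ratio when a strong predictor is left out.

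**Step 4. Schedule against coding.** The procedure names a single call, before the second SP dose. The model allows two and does not say what produces the second. The procedure also speaks of a sequence repeated until delivery, so calls might accumulate over visits. In that case women who stay in care longer could collect both more calls and more doses, and the bias could run upwards.

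**The case against.** The best defence is that this is a loosely worded, secondary process analysis in a condensed article. The outcome is not named and the word used is adjusting. The rule on components follows directly after the list of clinical outcomes, whereas the reminder aims at IPTp-SP uptake. A model of uptake could sit beside that rule. Home visits could also be added to the count and the model labelled exploratory.

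Part of this stands. A reader might infer several stronger points that the documents do not support:

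- **That calls are known to be confounded by reluctance.** No trigger for a second call is given, and the one call described is set by the calendar. Reachability follows from the text; reluctance is an assumption.
- **That coding home-visited women as 0 is a stated rule.** It is implied by counting calls only. Zero is fixed expressly for controls alone.
- **That one in five women will be unreachable.** The ownership figure is for adults in the area, and the Final study visit section plans to obtain a mobile number from each participant.
- **That the sections flatly contradict each other.** On a narrow reading, only component-against-component comparisons are barred. The fit is still poor, since the same sentence confines comparison to combined effects.
- **That a decision on keeping the reminder hangs on this model.** No section says so, and the feasibility outcomes list no reminder effect.

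What the defence does not remove is Step 1. The exposure and the control code are already fixed in the text, and no choice of outcome or covariates turns a count present in one arm only into a randomised reminder contrast. Counting home visits would repair the zero code but not that.

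**Conclusion.** The point holds in limited form. The call-count model uses a non-randomised exposure that arises after randomisation, and it cannot separate the reminder from screening and DHA-PQ, with or without a group term. Counting calls only also implicitly places women reminded at home among unreminded controls.

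The size is not fixed by the documents. Under the assumptions shown, the odds ratio per call with no true effect lies between 0.79 and 1.01 in model A. With a true group benefit it lies between 1.08 and 1.64. Reachability related to uptake was not simulated, and calls accumulating over visits could push the estimate upwards. It would therefore be wrong to say that the model must make a working reminder look useless or harmful.

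The primary comparison of placental malaria does not use call count and is untouched. This is a correction worth making to a secondary analysis and does not threaten the main result.

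**What to change.** 1. Do not use the call-count model to estimate a reminder effect.
2. Compare the number of IPTp-SP doses, and the proportion of women with at least three, between the groups as randomised. Label the result as the effect of the whole package, because this comparison does not isolate the reminder either.
3. Within the intervention group, tabulate how the reminder was delivered (call, home visit, none) as a description of delivery, with no effect estimate.
4. Reconcile the call schedule in the Intervention group section with the 0, 1, 2 coding in Statistical methods, and state what is counted.

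The cost is mostly wording. Doses are already monitored in both groups, and the planned model needs calls to be recorded anyway. Home visits would need a field in the reminder log if there is none. The downside is that no separate reminder estimate is reported, which the design cannot support in any case.

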### Dissemination plan

Dissemination of project results will target various audiences, including scientific communities, decision-makers, and public health authorities in Burkina Faso; health workers; and members of the public directly impacted by the results. A strategic plan will be prepared to support the mass dissemination of trial results to the various target audiences detailed above. A commitment to publish scientific results will be top of mind, with peer-reviewed open-access publications, a project-specific website, meetings, and conferences serving as avenues with which to share findings with various publics. EDCTP forums will be exploited. Clinical trial details will be shared on the ClinicalTrials.gov registry. Results will be disseminated via press releases and reports.

## Discussion

Successful control of malaria in pregnancy could save the lives of mothers and babies and is an essential part of antenatal care in endemic areas. In sub-Saharan Africa, many interventions such as IPTp-SP and ITNs have proven to be efficient at reducing malaria in pregnancy burden but adherence to recommended policies remains poor [33, 34]. There is then an urgent need to identify programmatic bottlenecks and gaps for optimal coverage of preventive and diagnostic tools. This study seeks to deliver preliminary results confirming the efficacy of the proposed intervention to reduce PM, peripheral malaria infection, and LBW. The present pilot study will also determine to which extent the randomized controlled trial is feasible in different settings within the fixed period of recruitment. Despite the high burden of malaria in pregnancy both pregnant women and their offsprings, no study has evaluated the impact of such combined interventions on placental malaria. Through this pilot study, study sites’ potential to complete the recruitment within the allocated period will be evaluated and adjustments will be made accordingly for the main trial. In addition, this pilot study will offer the opportunity to test all study documents such as informed consent, questionnaire, and standard operating procedure. Finally, the impact of the intervention on placental malaria will be demonstrated and current malaria in pregnancy prevalence gathered through this pilot. Malaria infection during pregnancy is often asymptomatic [35, 36] in high transmission areas while case management is based on the presence of signs and symptoms suggestive of malaria. In addition, many malaria cases are also missed in pregnant women due to the performance of the current RDTs, which are unable to detect low parasitemia. In the present study, we intend to improve the malaria case detection using monthly screening with US-RDT. We assume that US-RDTs will be able to detect all submicroscopic infections and that using DHA-PQ as antimalarial will help to clear all parasites. DHA-PQ has demonstrated good efficacy and safety profile combined with long post-treatment prophylaxis in a multicenter study conducted in Nanoro [26]. The number of women receiving at least 3 doses of IPTp-SP is below expectation. In such a situation, the qualitative behavioral study will be important as it will help understand barriers limiting uptake of IPTp-SP. The inner and outer setting process for implementation as well as the individuals involved will be explored. These investigations will add a great value and will help to improve significantly the prevention and control of MiP in Burkina Faso. Should the outcomes of this study be positive, it may be replicated on a large scale in order to see its impact in other malaria transmission areas. More specifically, socio-cultural factors that affect the uptake of MiP interventions will be identified and recommendations will be made to tackle them. The overall expected impact of this study will be specifically to reduce the adverse effects of MiP on both mothers and their offsprings.

### Trial status

The national ethic committee approved the study protocol version V0.1 BF on 02 September 2019. The recruitment started on August 31, 2020, and will cover a period of 1 year (in order to capture all variations due to seasonality) followed by 6 months of follow-up.

## Data Availability

The datasets used during the current study will be available from the corresponding author on reasonable request.

## Abbreviations

AL: Artemether-lumefantrine
ANC: Antenatal clinic
CERS: Comité d'ethique pour la recherche en santé
CHW: Community health workers
CRUN: Clinical Research Unit of Nanoro
DHA-PQ: Dihydroartemisinin–piperaquine
DSMB: Data safety monitoring board
HDSS: Health and Demographic Surveillance System
HRP-2: Histidine-rich protein-2
IPTp-SP: Intermittent preventive treatment in pregnancy with sulfadoxine-pyrimethamine
ITNs: Insecticide-treated nets
LBW: Low birth weight
MiP: Malaria in pregnancy
NMCP: National Malaria Control Program
PM: Placental malaria
RDT: Rapid diagnostic test
SAE: Serious adverse event
sSA: Sub-Saharan Africa
TSC: Trial Steering Committee
US-RDT: Ultrasensitive rapid diagnostic test
WHO: World Health Organization
